#### ​Group-level analysis

The case–control approach will be complemented by a group-level analysis of variance (ANOVA) of reaching accuracy, as measured by the PMI, with the between-subject factor of group (HC, MCI, AD) and the within-subject factor of side (non-dominant, dominant). This analysis will test whether the average severity of peripheral misreaching in each patient group significantly exceeds that observed in HCs.

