#### Analysis of single-case deficits

We will screen the control group for outliers that might suggest abnormalities, as such values would reduce the (already low, see figure 3) power to detect single-case deficits. We will use a robust method of outlier detection based on the median absolute deviation (MAD). The MAD can be multiplied by the consistency constant 1.4826 to estimate the SD, assuming a normal distribution. Each control participant’s PMI can be expressed as a modified Z-score (Z′) by subtracting the group median, divided by the MAD *1.4826. If Z′ exceeds 2.5 on either side, that participant will be excluded, and replaced. Our simulations suggest that, for a group size of 24, we would expect to exclude (on average)<1 participant (~0.67) by this criterion.

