### Radial reaching task

IRED speed is used to determine onset and offset of the reaching movement. Movement onset is defined as the first frame in which the IRED’s speed exceeds 50 mm/s (and maintains that speed for up to 100 ms). Movement offset is defined as the first subsequent frame in which IRED speed falls below 50 mm/s. The landing position of the movement is defined by the x-coordinate and y-coordinate in the final frame of the movement and will be recorded as errors relative to true target locations recorded during calibration for each participant.

An initial analysis of PMI for the radial reaching task will be performed, restricted to the two most eccentric target positions (33.4° and 43.6°). Case–control comparisons follow the plan for the lateral reaching task (Analysis of single case deficits section), to estimate the rates of peripheral misreaching, and borderline peripheral misreaching, in the two patient groups. Due to different experimental set-ups between the two test sites (UoE, UEA), each patient will be referenced to the same-site control data for case–control comparisons.

A group level ANOVA of PMI, restricted to the two most eccentric target positions, will similarly follow the plan for lateral reaching (Group-level analysis section). We will include site (UoE, UEA) as an additional covariate. More detailed analyses will also follow the plan for lateral reaching. Since motion tracking also provides kinematic variables on reaching trajectories, we also aim to examine the dependent variables peak speed and time to peak speed, normalised time after peak speed until reach endpoint and number of secondary movements.

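### Controls with a high PMI are removed and replaced but patients are not; if the trimmed controls form the HC arm of the group ANOVA, its false-positive rate is modestly above 0.05

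*Protocol article*

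**What the plan says.** Under 'Analysis of single-case deficits' the protocol article states: "We will screen the control group for outliers that might suggest abnormalities". The reason given concerns the single-case tests only: "as such values would reduce the (already low, see figure 3) power to detect single-case deficits". Each control's PMI becomes a modified Z-score, obtained "by subtracting the group median, divided by the MAD *1.4826"; the scaling constant is used "to estimate the SD, assuming a normal distribution". If the score exceeds 2.5 on either side, "that participant will be excluded, and replaced". The expected loss from a group of 24 is stated: "we would expect to exclude (on average)<1 participant (~0.67) by this criterion". No corresponding screen of patients is described.

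'Group-level analysis' then says that the single-case approach is "complemented by a group-level analysis of variance (ANOVA) of reaching accuracy, as measured by the PMI", with group (HC, MCI, AD) and side as factors, to test whether each patient group exceeds the controls. It does not name the control set, bring excluded controls back, or state an alpha level. Under 'Radial reaching task', the case-control comparisons follow the lateral plan, and the radial ANOVA "will similarly follow the plan for lateral reaching".

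**The concern.** A screen built for one analysis appears to carry over into another where it is not neutral. For the single-case tests, a tighter reference sample is the stated aim. For a comparison of group means, removing only the worst-performing controls while leaving equally extreme patients in place does two things. It pulls the HC mean down, and it makes the pooled error term too small. Both push towards finding patients worse than controls.

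If no group difference exists, the ANOVA would report one more often than its nominal rate, and the extra false positives would lie mostly in the direction the study hypothesises.

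**Working it through.** **Inputs.** From the article: 24 per group and three groups ('Power considerations'); cut-off 2.5 with the 1.4826 scaling, normality, and replacement of the whole participant ('Analysis of single-case deficits'); group-by-side ANOVA of PMI ('Group-level analysis'). Assumed, because the article gives no value: alpha 0.05 for the ANOVA, and a between-side PMI correlation ρ of 0 to 0.8. The article does not say whether replacements are screened in turn, so both cases are shown.

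**Step 1: the plan's own figure.** For each side, Z′ = (PMI − median) / (1.4826 × MAD). Simulated normal control groups of 24, counting participants with Z′ > 2.5 on at least one side, give:

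| Rule | ρ = 0 | ρ = 0.5 | ρ = 0.9 |
|---|---|---|---|
| High values only, either side | 0.667 | 0.64 | 0.535 |
| Absolute value, either side | 1.331 | 1.278 | 1.073 |

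The stated value of about 0.67 is reproduced by removing high values only. The absolute-value rule applied to both sides gives 1.07 or more.

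**Step 2: false-positive rate of the ANOVA.** Null trials were simulated with all three groups drawn from one normal distribution. Controls were screened (high values only) and replaced; patients were left alone. The group effect was tested on the side-averaged PMI (F on 2 and 69 df), and each patient group was compared with HC using the pooled error.

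| Control set | Omnibus F at 0.05 | Patients-worse tail of a two-sided 0.05 contrast |
|---|---|---|
| All controls kept | 0.049–0.052 | 0.025 |
| Screened, one round of replacement | 0.059–0.065 | 0.039–0.043 |
| Screened, replacements re-screened | 0.066–0.076 | 0.047–0.056 |

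Ranges cover ρ from 0 to 0.8. A separate set of 60,000 replicates per scenario gave 0.060–0.064 and 0.040–0.044 for one round, and 0.069–0.078 and 0.050–0.058 with re-screening. The third decimal should not be relied on.

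**Step 3: why so small a shift matters.** Take ρ = 0.5, one round, and a PMI SD of 1 on each side.

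- SD of the side average = √((1 + ρ)/2) = √0.75 = 0.866.
- SE of a patient-minus-HC difference = 0.866 × √(2/24) = 0.25.
- Simulated shift = 0.0497 side-average SDs = 0.0497 × 0.866 = 0.043 single-side SDs, which is 0.043/0.25 = 0.172 SE.
- Shift alone: upper tail = 1 − Φ(1.960 − 0.172) = 1 − Φ(1.788) ≈ 0.037, against 0.025.
- HC variance falls to about 0.91 of the patients', so the pooled variance is (0.91 + 1 + 1)/3 = 0.97 of its proper value. The tail becomes 1 − Φ(1.960 × √0.97 − 0.172) = 1 − Φ(1.758) ≈ 0.039.

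This approximation is rough. The simulation, which also carries the dependence between the trim and the sample, gives 0.044 for this case. Over all the normal scenarios the spurious difference is about 0.03 to 0.06 single-side SDs.

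**The case against.** **The screen belongs to the single-case section.** Its only stated purpose is single-case power, and the ANOVA section does not say which controls it uses. A reader might take it as stated fact that the trimmed group is the HC arm; it is an inference. It remains the plain reading, because exclusion and replacement are unqualified and no second control set is mentioned.

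**The trim may not be one-directional.** The wording does not say whether the sign of Z′ counts. An absolute-value rule counted on one side only gives 0.678 expected exclusions, also close to the stated figure, so Step 1 is good evidence but not proof. Under an absolute-value rule on both sides with normal data the mean shift vanishes. The understated control variance still leaves the omnibus rate at about 0.064 to 0.070 after one round, and up to 0.086 with re-screening.

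**Larger rates are tempting but not supported.** A one-sided 0.05 comparison of patients with HC would show about 0.08 after one round, but the article specifies one-tailed testing only for the individual case-control tests. Assuming right skew raises the rates further. However, the documents give no PMI distribution, the screen assumes normality, and skewness of 0.5 or 1 would imply about 1.16 or 1.82 exclusions rather than 0.67. Skew is plausible for a difference of absolute errors, but it shows only the direction of risk.

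**Screening controls alone has a rationale.** Controls are enrolled on reported health, so an extreme value might signal undetected impairment, whereas extreme values in patients are the signal under study. This stands, and is a reason to keep the screened analysis as a sensitivity analysis. Nor is the ANOVA the main analysis: the study is sized on the case-control and binomial tests. Under normality about 57% of control groups would lose nobody.

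**Conclusion.** The point holds in a limited form. If the screened controls are the HC arm, the ANOVA compares unscreened patients with a control group trimmed in the direction of the hypothesis. With normal PMI, 24 per group, an assumed alpha of 0.05, an assumed between-side correlation of 0 to 0.8 and one round of replacement, the omnibus error is about 0.06. That is roughly one extra false positive per 100 null trials. The error in the patients-worse direction is about 1.6 to 1.7 times nominal (0.039/0.025 to 0.043/0.025). With re-screening it is about twice nominal (0.047/0.025 = 1.9 to 0.056/0.025 = 2.2).

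The documents do not establish that the trimmed set is used, that replacements are re-screened, or that PMI is skewed. The radial ANOVA inherits the same issue by cross-reference but was not simulated separately. The main single-case and binomial analyses are outside this point. It is a modest correction to a supporting analysis.

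**What to change.** Add one sentence to 'Group-level analysis', and carry it to the radial task: the group ANOVAs include every eligible control who was tested, including any flagged by the Z′ screen. Confine the screen to the reference sample of the single-case tests. Report the ANOVA with screened controls as a sensitivity analysis. It would also help to state whether the sign of Z′ counts and whether replacements are screened in turn.

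With all controls kept, the simulated rates return to nominal (F 0.049 to 0.052; patients-worse tail 0.025). No new data are needed: 'Study setting' reports that control data are already collected, and flagged controls have been measured. With 8 of 48 patients tested at the time of writing, the rule could be fixed before most patient data existed.

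The cost is that a control with an undetected abnormality would stay in the HC group, widening its variance and pulling the comparison slightly towards the null. The sensitivity analysis would show this.

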#### Inclusion criteria

For all participant groups, the ability to give informed consent is the initial inclusion criterion. Additional inclusion criteria are then applied to each group.

Control group inclusion criteria:

Aged 50–75. (NB. The age-range for controls is targeted at the expected age range for patients, but the allowable range of ages for patients is wider than this, in order not to restrict recruitment unnecessarily.)No reported neurological or neurodegenerative conditions.

MCI group inclusion criteria:

Aged 45–85.Clinical diagnosis of MCI with an amnestic pattern of presentation. This includes an observed deficit on cognitive/neuropsychological testing suggesting amnestic and visuospatial profile deficit, low β-amyloid, elevated phosphorylated Tau, regional atrophy on magnetic resonance brain imaging and/or regional perfusion changes on HMPAO-SPECT (Single photon emission computed tomography with hexamethyl propylenamine oxime).

AD group inclusion criteria:

Aged 45–85.Clinical diagnosis of AD.

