**Figure 3 F3:**
[figure not shown]
Relation between(A) control sample size and power to detect a single-case deficit in a one-tailed test, for different sizes of deficit (D, expressed as SD of control mean). (B) D and power to detect a deficit, given a control sample size of 24, for adjusted (.025) and unadjusted (.05) alpha criteria.

We will next assess, for each side, whether the PMI of controls is related to age or sex, by computing Pearson’s correlations. If the correlation is ≥0.3 on either side, then that variable will be included as a covariate in the subsequent case–control comparisons for both sides.

Case–control comparisons will then be run to compare each patient’s PMI against control performance on each side of space. These comparisons will be based on Crawford and Howell's^15^ modified t-test; or, if covariates are included, we will use the Bayesian Test of Deficit with covariates.^16^ The individual tests will be one-tailed, with an alpha level set to 0.025, in order to constrain per-patient alpha level (across the two sides) to 0.05. If a patient shows a deficit on either side that meets the adjusted criterion (0.025), they will be classified as showing periperheral misreaching. If a patient shows a deficit on either side that would meet the unadjusted criterion (0.05), but not the adjusted criterion, they will be classified as showing borderline peripheral misreaching.

Finally, a binomial test will test whether the rate of observed peripheral misreaching exceeds the rate expected by chance (ie, the per-patient adjusted alpha level of 0.05). A significant outcome (p<0.05) for either patient group will indicate that peripheral misreaching is a feature of this patient group. The observed rate of peripheral misreaching will provide an estimate of how common it is. We will run a further analysis including borderline cases and compare the rate of peripheral misreaching in each patient group against the appropriate chance level of 0.10.

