#### Exploratory analyses

Any lateralisation that occurs in MCI/AD is likely to be limited, therefore, any impairment in peripheral reaching may be similarly non-lateralised. An average PMI (across both sides) will therefore be calculated to assess peripheral reaching ability overall. More detailed analyses will be run with a between-subject factor of group and within-subject factors of side, eccentricity and viewing condition. These analyses will be conducted using dependent variables of absolute reaching error, directional (signed) reaching error, reaction time and movement time. The expectation is that peripheral misreaching will manifest as a fixation-directed bias, which is exacerbated at higher eccentricities significantly more so in patient groups than in age-matched controls.

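### The group-level ANOVA has no age term although patients may be older than any control, so an age effect may be read as disease-related misreaching if the recruited patients prove older

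*Protocol article*

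**What the plan says.** All places are in the protocol article.

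- **Ages.** Inclusion criteria gives the control range as "Aged 50–75. (NB. The age-range for controls is targeted at the expected age range for patients" and adds that "the allowable range of ages for patients is wider than this, in order not to restrict recruitment unnecessarily". Both patient groups may be 45–85; the AD entry reads "Aged 45–85.Clinical diagnosis of AD".
- **Group model.** Group-level analysis specifies an ANOVA of PMI "with the between-subject factor of group (HC, MCI, AD) and the within-subject factor of side (non-dominant, dominant"). Its purpose is stated as: "This analysis will test whether the average severity of peripheral misreaching in each patient group significantly exceeds that observed in HCs". The Radial reaching task part of the analysis plan repeats this model for the two most eccentric targets and adds site. Age is in neither model.
- **Age rule elsewhere.** Analysis of single-case deficits correlates PMI with age and sex in controls. If the correlation is at least 0.3 on either side, "that variable will be included as a covariate in the subsequent case–control comparisons for both sides". Nothing extends this rule to the ANOVA.
- **Description of controls.** Exploratory analyses expects a fixation-directed bias "significantly more so in patient groups than in age-matched controls". No matching procedure is described.

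**The concern.** The plan treats age as a possible influence on PMI in one analysis and leaves it out of another analysis of the same outcome. Age could therefore pass the plan's own threshold, be adjusted for patient by patient, and still be ignored when group means are compared.

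The eligibility limits make an age difference possible. A patient aged 76–85 has no control of that age. Study setting says the control data are already collected, with 8 of 48 patients tested, so any imbalance now has to be handled mainly in the analysis.

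At stake is the interpretation of the severity comparison. If patients are older and PMI grows with age, a significant group effect cannot be attributed to MCI or AD rather than to age.

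**Working it through.** The plan gives no error rate or power for the ANOVA, so there is no figure of its own to reproduce here.

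**Inputs from the protocol.** 24 participants per group; three groups; controls 50–75 (midpoint 62.5); patients 45–85 (midpoint 65). The midpoints differ by 65 − 62.5 = 2.5 years.

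**Assumptions, not in the documents.** Age–PMI correlation r = 0.2 or 0.3; gap in mean age 0 to 10 years, the same for both patient groups; age uniform over 25 years in every group, so SD = 25/√12 = 7.2 years; a linear age effect; no disease effect; PMI averaged over the two sides, which is what the between-subject group test uses.

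**Step 1: spurious group difference.** In SD units of PMI, d = r × gap / 7.2. For r = 0.3 and 10 years, d = 0.3 × 10 / 7.2 = 0.42.

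**Step 2: false-positive rate of the group F test.** With both patient groups shifted by d, the noncentrality is 24 × [(2d/3)² + 2(d/3)²] = 16d². The test has 2 and 69 degrees of freedom and a 5% critical value of 3.13.

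| Gap (years) | d, r=0.2 | F-test rate, r=0.2 | d, r=0.3 | F-test rate, r=0.3 |
|---|---|---|---|---|
| 0 | 0 | 0.050 | 0 | 0.050 |
| 2.5 | 0.07 | 0.056 | 0.10 | 0.063 |
| 5 | 0.14 | 0.073 | 0.21 | 0.103 |
| 10 | 0.28 | 0.149 | 0.42 | 0.288 |

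Over r from 0.1 to 0.5 and gaps from 2.5 to 10 years, the rate runs from 0.051 to 0.678.

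**Step 3: effect of an age term.** Simulation with 4,000 runs per scenario, without and then with a linear age covariate:

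| r | Gap (years) | Without age | With age |
|---|---|---|---|
| 0.3 | 0 | 0.052 | 0.051 |
| 0.3 | 2.5 | 0.062 | 0.048 |
| 0.3 | 5 | 0.103 | 0.053 |
| 0.3 | 10 | 0.292 | 0.047 |
| 0.2 | 10 | 0.141 | 0.053 |

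The covariate returns the rate to about 0.05 in each scenario and does no harm when there is no gap.

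**Step 4: single-case tests under the plan's own rule.** Simulation of 24 controls uniform on 50–75 with an assumed side correlation of 0.5. Age is adjusted for when the control correlation reaches 0.3 on either side; a regression-based test stands in for the Bayesian test of deficit. Adjustment is triggered in about 47% of control samples at r = 0.2 and 69% at r = 0.3. The chance that an unimpaired patient is classified, against 5% intended, is:

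- about 7% at age 80 for either r;
- about 9% at age 85 for either r;
- about 5.5% averaged over patient ages uniform on 45–85;
- about 6% averaged over a patient group whose mean age is 10 years above that of controls.

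**The case against.** **The bias is not established.** A reader might infer that an age effect will be read as disease. That needs both a rise of PMI with age and an older patient sample, and the documents show neither. The control range was chosen with the expected patient ages in mind, patients may also be younger than any control (45 against 50), and the range midpoints differ by only 2.5 years, where the inflation is slight. This objection stands, and the point is conditional for that reason. Choosing a range is not matching, however, and it does not cover patients aged 76–85.

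**PMI already removes general factors.** The Tasks section subtracts free-reaching error so that general motor inaccuracy cancels. This stands for general motor decline. It does not remove an age effect specific to reaching in peripheral vision, and the plan's own age check on PMI accepts that one may remain.

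**The single-case tests.** A reader might also infer that 11% to 22% of unimpaired patients aged 80–85 would be classified as misreaching. Those rates arise only if age is never adjusted for (r = 0.2 to 0.3). The plan has an adjustment rule, and with it the rates fall to about 7% and 9%, and close to nominal over a whole group. The main binomial tests are therefore not seriously threatened on this ground.

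**Follow-up contrasts.** The stated aim compares each patient group with controls, while a three-group F test is not directional. The contrasts that follow an ANOVA are detail that an article may leave to the full plan, so no fault is claimed there.

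**Limited weight.** The ANOVA complements the case–control approach, and Power considerations rests the sample size on the case–control and binomial tests. This stands and limits the seriousness.

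**Conclusion.** The concern holds in conditional form. The group-level ANOVA omits age, the age limits differ between groups, and the plan treats age as a possible covariate for the same outcome elsewhere. If the patients recruited are older and PMI rises with age, the ANOVA cannot separate age from disease.

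The size depends on two quantities that the documents do not give. At an assumed correlation of 0.3, the inflation is negligible to small for a gap of up to 2.5 years (about 0.06), a doubling of the nominal rate at 5 years (0.10) and serious at 10 years (0.29). At 0.2 it is about half of the last figure (0.15 at 10 years). The single-case classifications, which carry the main inference, are largely protected. Calling the controls age-matched goes further than the recruitment rules support. The change is worth making because it is cheap and the plan already recognises the need for it in the other analysis.

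**What to change.** 1. Include age as a covariate in the group-level ANOVA of PMI for both the lateral and the radial task, fixed in advance and not dependent on the 0.3 threshold.
2. Report the age distribution of each group.
3. Pre-specify a sensitivity analysis limited to participants aged 50–75, where controls and patients overlap.
4. In Exploratory analyses, delete the description of controls as age-matched or support it with the age distributions.

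The cost is wording and a model term. Ethics and dissemination lists age among the patient details to be accessed, and the existing correlation check presupposes control ages, so no new data are needed. The ANOVA loses one degree of freedom (69 to 68 for error). For patients over 75 the adjustment extrapolates a straight line beyond the control data; the restricted sensitivity analysis addresses that, with fewer patients.

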### ​Specific hypothesis

The hypothesis that peripheral misreaching is a feature of AD means that individual patients with AD, and possibly those with mild cognitive impairment (MCI), may show an abnormally large inflation of reaching errors when aiming for targets in peripheral vision, as compared with targets in free vision. At a group level, patients with AD and, to a lesser extent, patients with MCI may show significantly greater peripheral misreaching than healthy controls (HCs).

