### Power considerations

The target sample sizes (N=24 per group) are based on power considerations related to the main inferential analyses, the case–control comparisons and binomial tests of rates of peripheral misreaching deficits for the lateral reaching task.

The control sample size of 24 will provide close to the maximum power for case–control tests of deficit (figure 3A). Note that high power for these comparisons is inherently unachievable unless the deficit being tested for is very large. We do not know how large any misreaching deficits may be in our patient groups, but our control sample size will provide close to the maximum achievable power to detect them if they exist. Figure 3B illustrates more fully the relationship between deficit size (D) and power, for the adjusted alpha level (0.025) and unadjusted alpha level (0.05) by which we will determine peripheral misreaching deficits and borderline cases, respectively (Analysis of single case deficits section).

The main hypothesis is that peripheral misreaching will be found in a significant proportion of patients with AD and MCI. For one-sample binomial test to determine whether the observed rate of peripheral misreaching exceeds the chance level of 0.05, a sample size of 24 has >0.9 power. Provided that the true population proportion is at least 0.2 (1 in 5). This is appropriate to our aims, since peripheral misreaching would be of limited significance in these clinical populations if its prevalence were less than 1 in 5.

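### The group-level ANOVA is credited with showing that each patient group exceeds controls, but its three-group F test cannot show that for either group; two planned contrasts against controls would

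*Protocol article*

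**What the plan says.** The Group-level analysis section of the protocol article specifies an ANOVA of PMI "with the between-subject factor of group (HC, MCI, AD) and the within-subject factor of side (non-dominant, dominant". It then states what this analysis is for: "This analysis will test whether the average severity of peripheral misreaching in each patient group significantly exceeds that observed in HCs". It names no contrast, no sidedness and no multiplicity rule.

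The Specific hypothesis section is directional and ordered at group level: "patients with AD and, to a lesser extent, patients with MCI may show significantly greater peripheral misreaching than healthy controls". For the neighbouring case-control tests, direction and multiplicity are fixed: "The individual tests will be one-tailed, with an alpha level set to 0.025", so that the two sides together cost 0.05 per patient. The Radial reaching task section carries the same ANOVA over, with site added as a covariate.

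**The concern.** The words chosen for the purpose of the ANOVA call for two comparisons, each with controls as reference and each with a direction. The group effect of a three-level factor is a test of any difference among three means. It takes no account of sign, it includes MCI versus AD, and a significant result does not say which group differs.

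Two things are at stake. First, a significant F could be reported as showing that both patient groups misreach more than controls when only one does, or when the difference runs the other way. Second, if pairwise comparisons are added afterwards, their sidedness, their adjustment and whether a significant F is needed first would all be chosen with the data in view.

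**Working it through.** **Inputs from the protocol.** Three groups, 24 per group (Power considerations). The ANOVA's alpha is not stated; 0.05 is assumed, the level used for the binomial test. No effect size is given: "We do not know how large any misreaching deficits may be in our patient groups". The protocol gives no power figure for the ANOVA, so there is none to reproduce.

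**Assumptions.** Shifts from HC in SD of side-averaged PMI, equal variances, and MCI at half the AD shift unless stated otherwise.

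**Step 1: what the group effect tests.** With two sides per participant, the group main effect is a one-way test on each participant's mean over sides. Degrees of freedom are 3 − 1 = 2 and 3 × 24 − 3 = 69; the 0.05 critical value is 3.13. Its power depends on λ = 24 × Σ(group mean − grand mean)².

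- AD +0.8, MCI +0.4: λ = 24 × (0.16 + 0 + 0.16) = 7.68, power 0.68.
- AD −0.8, MCI −0.4 (patients better than controls): the squares are the same, λ = 7.68, power again 0.68. At least one one-sided Dunnett contrast for patients above HC is significant in about 0.05% of simulated studies.
- AD +0.8, MCI equal to HC: λ = 24 × (0.0711 + 0.0711 + 0.2844) = 10.24, power 0.81, although MCI does not exceed HC at all.
- AD +0.8, MCI +0.4, by simulation: F is significant while the one-sided MCI-HC contrast is not in 40% of studies.

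**Step 2: power of the comparison actually wanted, AD versus HC.** The contrast t has 69 df and noncentrality d/√(2/24) = d/0.2887, which is 2.77 for d = 0.8. It does not depend on the MCI mean. Critical t: 1.95 for one-sided Dunnett and 2.26 for two-sided Dunnett (both simulated), and 2.40 for Tukey (studentized range for three means on 69 df, divided by √2).

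| AD / MCI shift (SD) | Omnibus F | Two-sided Dunnett, AD-HC | One-sided Dunnett, AD-HC |
|---|---|---|---|
| 0.6 / 0.3 | 0.43 | 0.43 | 0.56 |
| 0.8 / 0.4 | 0.68 | 0.70 | 0.79 |
| 1.0 / 0.5 | 0.87 | 0.88 | 0.93 |

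**Step 3: how much the unstated choices matter.** At 0.8 / 0.4 SD, the power to declare AD above HC is:

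- 0.63 for a significant F followed by Tukey
- 0.70 for two-sided Dunnett
- 0.78 for one-sided contrasts at 0.025 each (Bonferroni)
- 0.79 for one-sided Dunnett
- 0.86 for an unadjusted one-sided contrast at 0.05

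The span, 0.86 − 0.63 = 0.23, arises only from decisions that the plan leaves open.

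**Step 4: where the F does as well or better.** If MCI equals HC or AD at 0.8 SD, F power is 0.81, against 0.79 (one-sided) and 0.70 (two-sided) for the AD-HC contrast. At 0.6 SD the F has 0.55 against 0.56 one-sided. A significant F in these cases still does not identify which group differs or in which direction.

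**The case against.** The strongest reply is that the protocol never says the omnibus F is the test of each group. An ANOVA is ordinarily followed by comparisons from the same model, the reference to each patient group suggests this, and a journal article may leave such detail to a fuller plan. This stands in part: follow-up contrasts may well be intended. It does not remove the point, because the text assigns the conclusion to the ANOVA itself. The usual follow-up, all pairs after a significant F, is also a poorer answer than two contrasts with controls: its threshold of 2.40 exceeds 2.26, so it has less power for AD versus HC whatever the MCI mean.

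Three stronger readings are tempting and are not supported.

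- A reader might infer that the F in general costs power by spending it on MCI versus AD. Compared like with like, the loss against two-sided Dunnett is about 0 to 2 points under the protocol's ordering. Most of the apparent gain comes from one-sided testing, and the F is level or ahead when MCI coincides with HC or AD.
- A reader might infer that a significant F often arises with neither patient group above controls. Under the hypothesised ordering this happens in about 1.0% of studies at 0.6 / 0.3 SD and 0.5% at 0.8 / 0.4 SD.
- A reader might infer that the group analysis must be one-tailed because the case-control tests are. Nothing in the protocol requires that, and two-sided testing is an accepted convention.

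It is also fair that this analysis only complements the case-control approach. The main inferential analyses are the case-control and binomial tests, which already treat each patient group separately and in one direction.

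**Conclusion.** The point holds in a limited form. The mismatch between the named analysis and the stated conclusion is structural and needs no assumed effect size: a non-directional F on 2 degrees of freedom cannot show that either patient group exceeds controls.

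The numbers that illustrate it (68% rejection in either direction, 40% significant without MCI above HC, and 0.63 to 0.86 power for AD versus HC depending on unstated choices) rest on assumed shifts of 0.8 and 0.4 SD, equal variances and 24 per group. Other shifts would change them. The power gain over the F itself is small unless the contrasts are one-sided, and is not the reason for the change.

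Severity is modest. The analysis is secondary, the sample size was not set on it, and the main conclusions of the study do not depend on it.

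**What to change.** In the Group-level analysis section, state that the question is answered by two planned contrasts from the same model on side-averaged PMI, AD-HC and MCI-HC. They should be Dunnett-adjusted at family alpha 0.05, tested whether or not the group F is significant, and reported with confidence intervals. Keep the group F and the group-by-side interaction as supporting results. Use the same contrasts for the radial task, with site in the model.

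Fix the sidedness in advance. One-sided matches the directional hypothesis and the case-control tests, at the price of not formally testing a lower PMI in patients. Two-sided is also acceptable, with power of 0.70 rather than 0.79 for AD versus HC at 0.8 SD.

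The cost is a few sentences; no participants or measurements are added. The protocol reports 8 of 48 patients tested, so the change could be recorded while most patient data were still to come.
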